In the current pandemic, the impact of quarantine and physical distancing on the mental health of the general population has been explored only in a few studies, mostly conducted in China, where the pandemic started (23–25). Qiu et al. (26) found that 35% of the population experienced psychological distress; in particular, those more vulnerable to stress and more likely to develop post-traumatic stress disorder were women and individuals aged between 18 and 30 years or older than 60 years. Moreover, people were more concerned about their own health and that of their family members, while less concerned about leisure activities and relationships with friends (24, 27).

After China, Italy has been the first country to face the contagion of COVID-19 and one of the countries with the highest number of deaths due to this coronavirus (http://www.salute.gov.it/portale/nuovocoronavirus/). On March 8, the lockdown status has been declared by the Italian government. This status included the definition of specific containment and quarantine measures, such as the interdiction of all public meetings and strict movement restrictions (i.e., possibility to go out only for working, serious health reasons, or other urgent needs). These containment measures have been prolonged until May 4.

Moreover, the expected psychosocial and emotional reactions to the pandemic observed in the general population may be significantly different in the Chinese and Italian populations due to their socio-cultural characteristics and historical contexts, which obviously impact on people’s behaviors and attitudes. Furthermore, the organization of public health system is different in Italy compared to China and other Eastern Asian countries, also due to financial constraints. In fact, although in those countries the model of care has shifted in the last 20 years to become more similar to a Western model of care, it has to be acknowledged that 20 years is a relatively short period of time, and differences may still persist.

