### Data Collection

#### Recruitment Procedure

An online survey has been set up through EUSurvey, a web platform launched in 2013 by the European Commission. The application, hosted at the Department for digital services (DG DIGIT) of the European Commission, is available to all EU citizens at https://ec.europa.eu/eusurvey. The survey will be online from March 30 to June 30, 2020 (https://ec.europa.eu/eusurvey/runner/COVIDSurvey2020). The survey takes approximately 15–30 min to be completed. Participants can stop the survey at any time and save their answers as “draft” on the web-platform. Furthermore, participants can interact with the principal investigator of the study and with all researchers through email messages at any time during and after study participation.

Participants will be subdivided into four groups: a) Group 1—COVID-19 quarantine group. This group includes the general population which are quarantined but not isolated, i.e., those not directly exposed to contagion nor in contact with COVID-19+ individuals; b) Group 2—COVID-19+ group, which includes isolated people directly/indirectly exposed to the virus; c) Group 3—COVID-19 healthcare staff group, which includes first- and second-line healthcare professionals; d) Group 4—COVID-19 mental health, which includes users of mental health services and all those who had already been diagnosed with a mental disorder.

The survey addresses the Italian population aged over 18 years through a multistep procedure: 1) email invitation to health professionals and their patients; 2) dissemination of the link through social media channels (Facebook, Twitter, Instagram) and the mailing lists of national psychiatric associations; 3) involvement of national associations of stakeholders (e.g., associations of users/carers); 4) official communication channels (e.g., university websites; websites of the hospitals directly involved in the management of the pandemic).

The invitation letter includes information on study purposes and confidentiality. The provision of the informed consent is mandatory in order to start the survey.

The snowball sampling procedure—without the definition of strict inclusion/exclusion criteria (except that of age limit)—will give us the opportunity to recruit a large sample of the Italian population and to evaluate the effect of the studied variables on the outcome measures.

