### Data Analysis

Statistical analyses will be conducted according to a multistep plan. Missing data will be handled using the multiple imputation approach (47). Descriptive statistics will be calculated for the dependent and confounding variables. A bilateral alpha of 0.05 is considered, and error and confidence intervals are calculated at 95%.

The analytic plan will include: 1) data cleaning of the online dataset and replacement of missing values; 2) descriptive statistics of the general characteristics of the recruited sample, in terms of levels of depressive and anxiety symptoms, post-traumatic and stress-related symptoms, insomnia, satisfaction with life, suicidal ideation, hopelessness, post-traumatic growth, resilience, coping strategies, and social support; 3) sub-groups analyses based on the level of exposure to the pandemic (i.e., COVID-19 quarantine group vs. COVID-19+ patients group vs. COVID-19 healthcare staff group vs. COVID-19 mental health group); 4) calculation of a propensity score, in order to adjust our findings for the likelihood of being exposed to the pandemic and to the quarantine (48, 49). This method is adopted since it produces a better adjustment for differences at baseline, rather than simply including potential confounders in the multivariable models. The independent variables used for calculating the propensity score will include gender, age, socio-economic status, and geographical region. The obtained propensity score will be used to weight the observations in the multivariable analyses. In the final regression model, the inverse probability weights, based on the propensity score, will be applied in order to model for the independence between exposure to the pandemic/quarantine and mental health outcomes and estimation of causal effects (48, 49); 5) development of a Structural Equation Model (SEM), in order to evaluate the possible role as mediators and moderators of coping strategies, post-traumatic growth and usage of social networks on the severity of depressive and anxiety symptoms, post-traumatic and stress-related symptoms, suicidal ideation, and hopelessness.

In order to improve the external validity and generalizability of our findings, all analyses will be controlled for the impact of confounding variables, such as age, gender, and geographical region.

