We believe that our study has several strengths, which should be highlighted. First, this is the first national multicentric, no-profit study carried out in Italy with a rigorous methodology for evaluating the impact of pandemic and quarantine on mental health. Second, the development of a web-based platform for data collection will give us the opportunity to recruit a high number of participants. Based on previous population surveys carried out in Italy, an ideal target would have been 10,000 participants, but this target has been reached in only 7 days. Therefore, we expect to reach more than 20,000 people within the study period. A third relevant strength of our study is the selection of validated and reliable assessment instruments, which are available and validated in several languages. The next step of the project will be to adapt our survey to the European level, by involving several countries. Fourth, several psychopathological dimensions will be evaluated, not only those usually assessed following natural disasters, such as the post-traumatic and depressive-anxious dimensions. In this study, we will also evaluate the obsessive-compulsive spectrum, the suicidal ideation, the maladaptive use of Internet, among the others, which represent novel targets for psychiatrists (73, 74).

Our study has obviously also some limitations. In particular, the study sample includes the adult population only, due to existing restrictions related to the provision of informed consent of children and adolescents in Italy. However, it is likely that the pandemic will have a detrimental impact on the mental health of adolescents as well (75, 76). Moreover, being exposed to a traumatic event during early life is associated with alterations in the social, emotional, and cognitive development and could determine a variety of impairment in the adulthood. The effects of the pandemic on children and adolescents will be evaluated in an *ad hoc* study, in which we will explore the relationship between parents and their underage children during the pandemic. Another limitation is related to the recruitment process, which might partially bias our findings, since only persons interested in the topic of the survey may have voluntarily participated. However, we expect that most people are interested in participating in the survey given the global magnitude of the current traumatic threat with collective psychological and social reactions.

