Another possible limitation of our study is the choice to use a web-based online survey, which may have limited the participation of people not having access to the Internet or not familiar with online tools, particularly the elderly. The cross-sectional design of the study does not allow an evaluation of changes over time as regards the levels of severity of symptoms. However, in order to overcome this possible bias, we will compare our findings with those already available from the Italian population (46) and will adopt a propensity score approach in order to understand the impact of the duration of exposure to the pandemic on the risk of developing psychiatric symptoms. With this methodology, we will be able to evaluate the levels of post-traumatic growth and the type of resilience styles in the study population in order to identify possible critical areas to be targeted in the post-acute phase. However, these psychological constructs are slow to change, and this is why we will promote a second wave of the survey, which will start six months after the end of the “lockdown phase” in Italy. Finally, the survey link can be used multiple times in order to allow sharing and re-posting it. This methodological choice could bias the findings, since the same person can potentially compile the survey several times. However, this methodological choice was due to the adoption of the “snowball” sampling, and it is rather unlikely that someone can compile the same long survey more than once.

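### Time since lockdown is fixed by response date, so the planned propensity score cannot separate duration of exposure from a changing mix of responders and does not overcome the cross-sectional limit

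*Protocol article*

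**What the plan says.** The Discussion (limitations) admits: "The cross-sectional design of the study does not allow an evaluation of changes over time as regards the levels of severity of symptoms". It offers two remedies: comparison with earlier Italian data, and a propensity score. On the second, the authors say they "will adopt a propensity score approach in order to understand the impact of the duration of exposure to the pandemic".

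The passages that bear on whether the score can do this are:

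- **Background**, start of exposure: "On March 8, the lockdown status has been declared by the Italian government". End of exposure: "These containment measures have been prolonged until May 4".
- **Recruitment Procedure**, survey window: "The survey will be online from March 30 to June 30, 2020". Sampling is by open snowball. The channels include "email invitation to health professionals and their patients", social media, psychiatric mailing lists, user and carer associations, and institutional websites.
- **Data Analysis**, the score: it adjusts for the likelihood of being exposed to the pandemic and quarantine, and the weights are meant to support causal estimates. "The independent variables used for calculating the propensity score will include gender, age, socio-economic status, and geographical region".
- **Discussion**, accrual: "an ideal target would have been 10,000 participants, but this target has been reached in only 7 days". More than 20,000 respondents are expected in all.
- **Exploratory Outcomes**: exposure time is to be tested as a possible mediator of symptom severity.

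**The concern.** A propensity score can balance measured differences between people whose exposure differs. It cannot create variation in exposure that is independent of when a person answered.

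All residents share one lockdown start and each normally answers once. A person with long exposure to the lockdown is therefore simply someone who answered late. Any feature that makes people answer early or late, and that also relates to symptoms, will look like an effect of duration unless it is in the weighting model. The four named variables are demographic. They do not cover healthcare occupation, prior mental disorder or motivation to respond.

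The easing of measures is a second problem. Late responders have been exposed for longer and are also answering under relaxed restrictions, and no weighting on personal characteristics separates the two.

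What is at stake is the reading of the duration result. With a sample this large, a small change in who responds could be reported as symptoms rising or falling with exposure, in an analysis whose weights are said to support causal effects.

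**Working it through.** **Inputs from the article.** Lockdown start 8 March; end of measures 4 May; survey 30 March to 30 June 2020; 10,000 responses in 7 days; more than 20,000 expected; two-sided alpha 0.05. I take the 7 days to be the first week of the survey. The article gives no SD, effect size or sample-size formula, so 10,000 and 20,000 cannot be reproduced, only used.

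**Step 1. Duration against response date.**
- Window: 2 + 30 + 31 + 30 = 93 days.
- Days since 8 March: 22 on 30 March, 28 at the end of the first week, 114 on 30 June.
- Everyone answering on a given date has the same time since lockdown.

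**Step 2. Front-loading.**
- 7/93 = 7.5% of the window gave 10,000 responses.
- Share of the total: 10,000/20,000 = 50%; 40% if 25,000 respond; 33% if 30,000. About half is thus the upper end.
- Daily rate: 10,000/7 = 1,429 in week 1. Over the other 86 days it is 10,000/86 = 116, a 12.3-fold drop. With 30,000 respondents it is 20,000/86 = 233, a 6.1-fold drop.

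**Step 3. Easing of measures.**
- Survey days after 4 May: 27 + 30 = 57, and 57/93 = 61%.
- This is a share of days, not of people. At a total of 20,000 and an even rate after week 1 (an assumption), 57 × 116.3 ≈ 6,630 people, about a third, would answer after 4 May.

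**Step 4. Size of a spurious effect (assumed inputs, no true duration effect).** Take 10,000 early and 10,000 late responders.
- Bias = (change in share of an unadjusted responder type) × (its score difference in SD).
- SE = √(2/10,000) = 0.0141 SD.
- Difference detectable with 80% power: (1.96 + 0.84) × 0.0141 = 0.040 SD.
- Chance of significance in the direction of the shift: Φ(bias/SE − 1.96).

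| Shift in share | Score gap | Bias | Significant |
|---|---|---|---|
| 2 points | 0.3 SD | 0.006 SD | 6% |
| 5 points | 0.5 SD | 0.025 SD | 42% |
| 5 points | 0.8 SD | 0.040 SD | 81% |
| 10 points | 0.5 SD | 0.050 SD | 94% |

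**Step 5. Does weighting remove it?** A 300-run simulation applied inverse probability weights from four covariates standing for gender, age, socio-economic status and region. It was generous to the plan, because the score was built for early against late response. The unadjusted responder type was unrelated to the four covariates within wave.
- 5 points at 0.5 SD: bias 0.025 SD, 40% significant.
- 10 points at 0.5 SD: bias 0.051 SD, 92% significant.
- No shift in the unadjusted type: bias about 0, 6% significant.

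The weights dealt with the covariates they contained and left the rest of the bias in place.

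**The case against.** The other side has several good points.

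- **The groups already separate the obvious drivers.** People with a prior mental disorder form Group 4 and healthcare staff form Group 3, and the Discussion says analyses follow the four groups. A reader might infer a large artefact from a falling share of psychiatric patients: 15% early against 5% late, 1 SD apart, gives 0.10 SD and z = 0.10/0.0141 ≈ 7. The documents do not support that. The shift is invented, and analysis within groups would largely remove it. What remains is that the article does not say the duration analysis is run within group, and that mix can also shift inside a group.
- **Staggered recruitment is an inference.** The article numbers the channels of a multistep procedure but gives no dates, so it does not establish that professionals and patients came first. A changing mix is plausible, not shown.
- **Duration is not defined.** For isolated people and first-line staff, exposure time could be dated individually and vary among people answering on the same day. The point therefore bites most clearly in Group 1. The quoted sentence does, however, concern exposure to the pandemic.
- **The covariate lists may be open.** The score will include the four variables, other confounders are introduced by example, and a fuller list may exist elsewhere. Even so, the score is described as one for likelihood of exposure, and a longer list would not separate duration from the easing of measures.
- **Limits are acknowledged.** Self-selection is admitted, but only as interest in the topic, not as something that changes over the window. The second survey wave is motivated by slow-changing constructs and is not described as following the same people.

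**Conclusion.** The concern holds as a criticism of one claim and one exploratory analysis. On the article's own dates, time since lockdown is determined by response date, and late response is tied to the easing of measures. The described score addresses neither, so it does not overcome the cross-sectional limit.

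The size and direction of any bias are unknown, because the article has no data on how the mix changes. The conditional range runs from negligible (2 points at 0.3 SD) to 0.05 SD, significant in 94% of studies (10 points at 0.5 SD). These figures assume 10,000 per wave, a responder type not captured by the weights, and a pooled early-against-late contrast that the article does not itself specify.

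A reader might also infer that the main findings are compromised. They are not directly affected: the primary DASS-21 comparisons, with a community sample and between groups, do not rest on exposure time.

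**What to change.** 1. Estimate the duration trend separately within each of the four groups, and say so.
2. For any pooled duration analysis, model duration or response week itself instead of likelihood of exposure. Add prior mental disorder and healthcare occupation to the weighting variables; both are needed to form the groups, so no new data are required.
3. In the Discussion, replace the claim that the propensity approach overcomes the cross-sectional limit. State that response date is confounded with responder mix and with the easing of measures after 4 May, and that the trend is descriptive.

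A new survey item on recruitment route is not worth adding: it would be missing for the first 10,000 respondents, the very wave being contrasted.

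The cost is analysis wording, somewhat more variable weights and a weaker stated conclusion. Neither the design nor the primary analysis changes.

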### Next Steps

Based on the findings of this study and on our previous work in the development of psychosocial interventions (77–79), we aim to develop a psychosocial intervention which will include elements of classic psychoeducation, cognitive-behavioral therapy, and motivational intervention (80–84). In particular, we are developing an experimental intervention which includes information on the mental health consequences of the pandemic and on strategies to prevent them; practical advices for promoting healthy lifestyle behaviors (e.g., healthy eating, regular sleeping patterns, physical activity, etc.); stress-management techniques; communication strategies; problem-solving skills. Based on participants’ needs, additional sessions on suicide prevention, burn-out, and Internet dependence may be provided.

The intervention will include face-to-face sessions and tele-mental health sessions (85, 86). Information will be provided through instant messages (e.g., Chatbot), email contacts, and the development of an *ad hoc* app.

The modules of the intervention will be adapted according to the characteristics and the needs of the four above-mentioned target groups. In particular, in the COVID-19 quarantine group, the main focus of the intervention will be the improvement of healthy lifestyle behaviors; for the COVID-19+ patients group, the intervention will include a specific focus on post-traumatic symptoms and on the risk of being socially stigmatized; for the COVID-19 healthcare staff group, specific sessions will be dedicated to the burn-out syndrome and the management of stressful situations; for the COVID-19 mental health group, sessions on resilience, coping strategies, and the detection of early warning signs of relapses will be included.

The proposed experimental intervention will be tested in a randomized controlled trial which will start when the acute phase of the pandemic will be over, and the control group will be represented by an informative group intervention on the effects of the pandemic on mental health.

Moreover, our survey is going to be translated into different languages in order to assess the impact of the pandemic in other European countries.

## Conclusions

The pandemic and the quarantine may have a detrimental impact on mental health. An increase of psychiatric symptoms and of mental health problems in the general population is expected. Most health professionals working in isolation units and resuscitation departments very often do not receive any training or support for their mental health care. Mental health services worldwide are not prepared to manage the short- and long-term consequences of pandemic. It is necessary to have a clear picture of the impact that these new stressors are having on mental health and well-being in order to develop and disseminate appropriate preventive interventions for the general population as well as for the different at-risk groups.

## Ethics Statement

This study is being conducted in accordance with globally accepted standards of good practice, in agreement with the Declaration of Helsinki and with local regulations. The study protocol has been approved by the Ethical Review Board of the University of Campania “L. Vanvitelli” (Protocol number: 0007593/i).
